## Methods/design

### Study design and setting

The study CogTrAiL-RBD is designed as a monocentric, single-blinded, delayed-start randomized controlled trial with two study arms aiming to consecutively recruit 80 individuals with iRBD confirmed by polysomnography from the continuously expanding local iRBD cohort at the University Hospital Cologne in Germany [54]. Participants will be randomly assigned to either the early intervention group or a delayed-start control group. Forty participants will be randomly assigned to each group (parallel group phase, superiority). The delayed-start control group will receive the same intervention after a 6-month waiting period, with the early intervention group undergoing the intervention for a second time to separate symptomatic from potentially disease-modifying effects (open-label phase, exploratory) [55].

Figure A-1 presents the schematic trial design and Appendix Figure A-1 further illustrates the timeline for participants. At baseline assessment (t0, week 0), the study will be explained to the participants. Subsequently, the participants will provide written informed consent and answer to a demographic interview. All participants with iRBD will undergo comprehensive clinical and neuropsychological assessments at the t0 visit and 6 weeks post allocation (posttest I, t1, week 6). A follow-up assessment (follow-up I, t2, week 33) will be conducted after 6 months. Subsequently, the second intervention phase for both the early intervention group and the delayed-start control group begins, followed by another clinical and neuropsychological assessment (posttest II, t3, week 39). Finally, a follow-up assessment (follow-up II, t4, week 66) will take place after an additional 6 months.

There are three optional study modules for individuals with iRBD that accompany the mandatory clinical and neuropsychological assessments: (i) the MRI module consisting of structural and functional MRI at each assessment time point; (ii) the accelerometry module consisting of physical activity tracking with accelerometers at each assessment time point; and (iii) the polysomnography module including two polysomnographies, one before the start of the intervention and one within the last 2 weeks of the intervention. Additionally, an age- and sex-matched HC group will be examined at the first assessment time point, participating in the comprehensive clinical and neuropsychological assessments, the MRI module and the accelerometry module.

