For the analysis of training effects in the primary and secondary outcomes, linear mixed effects (LME) models will be used. Dependent variables are the respective primary or secondary outcome measures. All dependent variables are assessed at three points of time. The LME models include time (t0, t1, t2), group (early intervention group and delayed-start control group), and the interaction between time and group (time*group) as fixed factors. Furthermore, participants and time are included as random factors. Models will be estimated using the *lmer()* function of the *lme4*-package employing restricted maximum likelihood estimation [119]. Model fit will be evaluated using marginal *R*^2^, which considers the variance of the fixed effects only, and conditional *R*^2^, which accounts for both fixed and random effects. *t*-Tests will be conducted to assess the significance of single coefficients. For the interaction effects, relative effect sizes with 95% confidence intervals will be reported and defined as the difference of the mean change over time in the early intervention group minus mean change over time in the delayed-start control group divided by the pooled baseline standard deviation of the cohort. Within the analysis of training effects, we will pursue an intention-to-treat approach. No imputation methods will be used, as one strength of LME models is their ability to deal with unbalanced designs, for example, due to missing values in longitudinal data.

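### Time (t0, t1, t2) is declared both a three-level fixed factor and a random factor: the random structure of the primary model is unidentifiable or ambiguous, and the literal version that runs gives the t1 and t2 contrasts one common standard error

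*Protocol article*

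**What the plan says.** The protocol article, Statistical analyses, gives the fixed part as follows: "The LME models include time (t0, t1, t2), group (early intervention group and delayed-start control group), and the interaction between time and group". It adds "All dependent variables are assessed at three points of time", and then, for the random part, "Furthermore, participants and time are included as random factors". On software it says "Models will be estimated using the *lmer()* function of the *lme4*-package employing restricted maximum likelihood estimation". Single coefficients are t-tested, and marginal and conditional R-squared are to be reported. The training effect is expressed through the interaction, as a difference in mean change between arms divided by the pooled baseline standard deviation.

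No model formula is printed. The text does not say whether the random time term is a crossed intercept, a by-participant factor or a by-participant slope on a numeric time variable.

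Study design and setting puts baseline at week 0, the first posttest at week 6 ("posttest I, t1, week 6") and the first follow-up at week 33. Sample size and power calculation gives one baseline-retest correlation, 0.8, and none by visit. Statistical analyses says that the article reports the primary and secondary analyses of the parallel-group phase. It announces separate plans only for exploratory outcomes and analyses.

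**The concern.** A factor whose three levels are already fully represented by fixed effects leaves nothing from which to estimate a random variance for those same levels. Taken literally, the sentence therefore describes a model with an unidentifiable component. Taken loosely, it could mean any of several models, and these give different standard errors for the interaction coefficients that carry the treatment effect.

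Two things are at stake. The first is prespecification of the primary model: whoever runs it must decide what the sentence means. The second is the validity of the t1 and t2 tests. The crossed version amounts, for those tests, to a random intercept, which assumes the same correlation between any two visits although they are 6, 27 and 33 weeks apart.

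**Working it through.** **1. The plan's own figures.** 64 × √(1 − 0.8²) = 64 × 0.6 = 38.4, taken as 38 per group; 2 × 38 = 76; 76/0.95 = 80. These reproduce. The article gives no figure for the mixed model itself. Carried forward: 40 per arm, and 80 × 3 = 240 observations per outcome.

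**2. Crossed random time, (1|participant) + (1|time).** The fixed design has rank 6 with or without the time indicators, so the random time effects lie wholly inside it. On simulated 80 × 3 data, the REML log-likelihood is identical for a time variance v of 0, 0.01, 0.1, 1 and 10. With residual variance 0.23 and 40 per arm:
- SE of a time coefficient = √(2 × 0.23/40 + 2v): 0.107 at v = 0, 0.460 at 0.1, 1.418 at 1, 4.473 at 10.
- SE of a time-by-group coefficient = √(4 × 0.23/40) = 0.1517 at every v. A visit effect shared by both arms cancels in the between-arm difference.

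An actual lmer fit warns that the model is nearly unidentifiable and stops at an arbitrary v of 0.0016. The time coefficients then have SE 0.1216, against 0.1072 without the term, and zero Satterthwaite degrees of freedom. The interaction estimates and SEs (0.1516) are the same in both fits. Marginal and conditional R-squared inherit the arbitrary v through the total variance.

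**3. Time as a by-participant factor, (time|participant).** This has 80 × 3 = 240 random effects for 240 observations, and lmer stops with an error by default. (1|participant:time) also stops.

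**4. By-participant slope on numeric time.** It has four covariance parameters, all identified (Jacobian rank 4 of 4) whether time is 0, 1, 2 or weeks 0, 6, 33, and lmer fits it. In one simulated data set, for illustration only, the t2 interaction estimate was −0.301 throughout:

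| Random part | SE at t1 | SE at t2 | p at t2 |
|---|---|---|---|
| Intercept (same as crossed) | 0.152 | 0.152 | 0.049 |
| Slope on visit number | 0.141 | 0.170 | 0.081 |
| Slope on weeks | 0.135 | 0.164 | 0.070 |

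**5. Size of the common-SE problem.** Assume unit variance at each visit, 40 per arm and complete data. Let ρ̄ be the mean of the three correlations.
- Random-intercept SE, same for both contrasts: √(4(1 − ρ̄)/40).
- True SE of the contrast at visit k: √(4(1 − ρ0k)/40).
- Type I error: 2 × [1 − Φ(1.96 × model SE/true SE)].

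Example, 0.85/0.75/0.80 (t0-t1/t0-t2/t1-t2): ρ̄ = 0.80 and model SE = √0.02 = 0.1414. True SEs are √0.015 = 0.1225 and √0.025 = 0.1581. The ratios are 1.155 and 0.894, so type I error is 2.4% at t1 and 8.0% at t2.

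| Assumed correlations | SE ratio t1 / t2 | Type I error t1 / t2 |
|---|---|---|
| 0.80/0.80/0.80 | 1.00 / 1.00 | 5.0% / 5.0% |
| 0.80/0.75/0.80 | 1.04 / 0.93 | 4.1% / 6.8% |
| 0.80/0.70/0.80 | 1.08 / 0.88 | 3.4% / 8.4% |
| 0.85/0.75/0.80 | 1.155 / 0.894 | 2.4% / 8.0% |
| 0.85/0.70/0.75 | 1.25 / 0.88 | 1.5% / 8.4% |
| 0.80/0.60/0.80 | 1.155 / 0.816 | 2.4% / 11.0% |

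Simulation with 40,000 runs agrees: 5.1%/5.0% in the first row and 2.5%/11.1% in the last. The ratios do not depend on the number per arm. All the correlations are assumptions.

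**The case against.** The case on the other side is substantial.

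- A reader might infer that the primary model cannot be run. That is too strong. The crossed form returns a fit, and its interaction SEs do not depend on the arbitrary variance. A numeric slope is identifiable, and condensed prose may have meant exactly that.
- The by-participant factor error is an input check that can be switched off. On simulated data with correlations 0.85/0.70/0.75 and the check off, lmer gave convergence warnings. Its interaction SEs were 0.11915 and 0.17092, against 0.11915 and 0.17093 from direct change-score regressions. Only the split between residual and random variance is unidentified, and the implied covariance is unstructured.
- A reader might infer that the plan contains a random-intercept fallback. It names none. The random intercept enters only because the crossed reading is equivalent to it for the interaction.
- A reader might infer that the trial's type I error is 8% or 11%. The documents give no correlation by visit, and under equal variances and correlations there is no error at all.
- An article may leave the exact formula to a fuller document, and it can still be fixed before the data are analysed.

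All of this limits the consequence. It does not rescue the sentence. The article says that it reports the primary analysis, and it states a random factor that the fixed part already absorbs. The readings that remain give different SEs for the same coefficient.

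**Conclusion.** The point holds at moderate severity. Read as a random factor, time duplicates the fixed factor and adds a component that the data cannot identify. In the crossed form the damage falls on the intercept, the time main effects and R-squared. The treatment contrasts are then those of a random-intercept model.

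That model is valid for both contrasts only if variances and correlations are equal across weeks 0, 6 and 33. With equal variances and correlation falling as the gap widens, it is conservative at t1 and anti-conservative at t2. Over the assumed grid, type I error lies between 1.5% and 5% at t1 and between 5% and 11% at t2. The direction rests on the assumed decay and the size on assumed values. The sample size is untouched.

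**What to change.** Before the t2 analysis, delete time as a random factor. Prespecify a repeated-measures model with categorical time, group and their interaction, and an unstructured within-participant covariance, for example with mmrm or nlme::gls. Use Satterthwaite or Kenward-Roger degrees of freedom. This model remains valid under every correlation pattern in the table above.

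If lmer is kept, the minimum is to print the exact formula and the coding of time. If a random intercept alone is chosen, the text should state that it assumes equal correlation across weeks 0, 6 and 33.

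The cost is one paragraph of analysis text, a different R function, and six covariance parameters (three variances and three correlations) against two for a random intercept. No change to recruitment or visits is needed.

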### Dissemination plans

The results of CogTrAiL-RBD will be published in international, peer-reviewed scientific journals and presented at national and international conferences. Following the main publication of the behavioral effects of the training including the training effect on the primary outcome of executive functions, results will be disseminated to participants via email in a way that is easily understandable for non-experts. If any important protocol modifications occur, they will be communicated in a written form to relevant parties.

## Discussion

CogTrAiL-RBD is to the best of our knowledge the first cognitive intervention study, additionally promoting a healthy, active lifestyle, for individuals with iRBD. With the longitudinal, multi-modal data collection, it will not only be possible to gain insights on the effectiveness of such an intervention at this at-risk group for the development of PD, DLB, and MSA and corresponding cognitive impairment, but we will also develop a better understanding on the underlying mechanisms of behavioral training effects. The trial is powered to detect behavioral differences in the first parallel-group phase of the randomized controlled trial. Following, any analyses focusing on the second open-label phase are fully exploratory, constituting a limitation to the trial. From a clinicians’ and patients’ perspective, this trial is pioneering, as it could alleviate ethical concerns associated with an early iRBD diagnosis [27–29]. Cognitive training combined with psychoeducation on a healthy, active lifestyle would be a low-threshold and safe intervention approach for this at-risk group to counteract cognitive decline.

## Trial status

The trial status is ongoing with the first participant included on June 14, 2022. We expect the recruitment to be finished by June 2024. At the time of revision (May 10, 2024), 85% (*n* = 68) of the participants with iRBD planned to be included (*N* = 80) were recruited, with 68.75% (*n* = 55) already being enrolled in the trial. At baseline t0, the current participation score in the MRI module is 54.5% (*n* = 30), of which 56.7% (*n* = 17) were also willing to participate in the polysomnography module. The participation score for the accelerometry module is as high as 96.4% (*n* = 53) at baseline t0. The protocol version is V5 as of 2023–04-24.

## Data Availability

Beyond the registration in the German Clinical Trial Register (Identifier: DRKS00024898), CogTrAiL-RBD is registered in the Open Science Framework (OSF, https://osf.io/). The OSF will be used as a platform to make our data and corresponding material available. Following the publication of corresponding manuscripts, we aim to share the anonymized individual participant data (IPD) according to the FAIR principle—findable, accessible, interoperable, reusable. All data sharing will only be undertaken in accordance to legal requirements. A model consent form is displayed in Appendix B-2.

## Abbreviations

CogTrAiL-RBD: Cognitive Training and a Healthy, Active Lifestyle Program for Patients with isolated REM Sleep Behavior Disorder
DLB: Dementia with Lewy bodies
HC: Healthy control individuals
ICC: Intraclass correlation
iRBD: Isolated REM (rapid eye movement) sleep behavior disorder
IPAQ: International Physical Activities Questionnaire
LAQ: Lifestyle Activities Questionnaire
MDS-UPDRS-III: Movement Disorder Society Unified Parkinson’s Disease Rating Scale Part III
MEDAS: Mediterranean Diet Adherence Screener (MEDAS)
MRI: Magnetic resonance imaging
MSA: Multiple system atrophy
OSF: Open Science Framework
PD: Parkinson’s disease
PDD: Parkinson’s disease dementia
PR: Percentage ranks
RBD: REM (rapid eye movement) sleep behavior disorder
SPIRIT: Standard Protocol Items: Recommendations for Interventional Trials
TE: Echo time
TR: Repetition time
